**Figure 2 figure2:**
[figure not shown]
Study flow diagram.

### Multiarm Trial Rationale

The six study arms were developed to explore the individual and combined effects of behavioral prompts grounded in behavioral economics, to identify which strategies most effectively enhance engagement in a digital resiliency program. Each arm includes a specific configuration of tips, checklists, or gamification elements intended to test distinct motivational mechanisms. This design enables comparative analysis across different engagement strategies while remaining operationally feasible. These components tested include (1) directive tips, grounded in the theory of implementation intentions, which provide straightforward, actionable guidance; (2) social proof tips, which leverage peer effects by referencing the behavior of others to encourage participation; (3) present bias tips, designed to counteract temporal discounting by emphasizing short-term benefits of engagement; (4) to-do checklists, which introduce structured goals and progress-tracking to increase adherence; and (5) gamification, which builds intrinsic motivation through visual indicators of advancement and progress feedback.

While a full factorial design could have explored all possible combinations of these interventions, the current 6-arm structure is a deliberate balance between conceptual rigor and practical feasibility. This structure enables comparative analysis across a diverse set of nudge combinations without creating an unmanageable number of trial arms. It was also informed by operational constraints and the need for meaningful data distribution across arms.

Our study design is also a foundational step toward developing a predictive analytics dataset. The behavioral engagement data collected through the six arms will be used to build baseline models that inform AI-driven personalization strategies. Future iterations of the course will be updated with tailored nudges based on user profiles, and new user data will be used to validate and refine the models. We chose the current design to generate sufficient diversity and volume in behavioral data to create a baseline for our long-term, adaptive research agenda.

### Primary and Secondary Outcomes

The primary outcome is engagement with behavioral prompts, defined as whether a user clicks on a specific tip, type of tip, or checklist item and is directed to the associated course component (refer to Table 3). This outcome reflects the initial behavioral response to a specific nudge. It serves as the basis for understanding which types of prompts are most effective at initiating action within the course. Secondary outcomes reflect broader patterns of use and progression through the course. These include (1) completion of main course components (eg, submitting a goal, completing the depression and anxiety test, completing course sessions, and engaging with other tools defined in Table 3); (2) click rate, defined as the proportion of tips and checklist items clicked; (3) session duration, or the total time spent on the platform; and (4) number of course sessions completed, including badge acquisitions and quiz completions.

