#### Behavioral Prompts

Behavioral prompts are cues specifically designed to encourage a specific task [58]. In this study, we will use 2 types of behavioral prompts anchored in nudge theory: daily tips and a to-do checklist (Table 1). These prompts are intended to support self-guided action, reinforcing positive behavior without requiring direct human intervention.

An effective approach for boosting user involvement in digital health interventions may be offered by analyzing combinations of behavioral prompts that users engage with. Through machine learning techniques, the dataset emerging from this study may provide insight into which and what prompts work best with specific demographics and usage patterns [59]. By customizing interventions to meet the unique needs of every user, this integrated approach might increase the possibility of long-term behavior change and better health outcomes.

**Table 1 table1:** Example nudges and prompts.

Delivery format	Content type	Example from our study
Tip	Directive content	Express yourself by uploading your image!
Tip	Social proof	Many members have similar goals to yours. Reviewing other members’ goals can help you reach your goal.
Tip	Present bias	Feel better sooner by learning from others. Read what others have posted in the community.
Prompt	To-do checklist	Watch the getting started video.
Visual element	Gamification	A progress bar fills as users complete sections of the course.

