### Our Prior Work

We have experimented with nudges and prompts in the past. In our previous 3-arm randomized controlled trial (RCT) [24], arm 1 featured a member home page without nudges or prompts. Arm 2 featured a home page with a tip-of-the-day section. Arm 3 featured a home page with a tip-of-the-day section and a to-do checklist.

Control arm members (1788/13,224, 13.52%) completed an average of 1.5 course components. Arm 2 members (865/13,224, 6.54%) clicked on 5% of tips and completed an average of 1.8 course components. Arm 3 members (1914/13,224, 14.47%) clicked on 5% of tips, completed 2.7 of 8 to-do checklist items, and an average of 2.11 course components. Completion rates in arm 2 were greater than those in arm 1 (*z* score=3.37; *P*<.001), and completion rates in arm 3 were greater than those in arm 1 (*z* score=12.23; *P*<.001). Engagement in all 8 components in arm 3 was higher than that in arm 2 (*z* score=1.31; *P*<.001).

Further analysis confirmed that behavioral economics techniques, such as nudges and prompts, significantly enhance engagement in digital health interventions. Specifically, users in the nudge + prompt condition (arm 3) were 93% more likely to engage compared to those in the control group (arm 1), as indicated by an odds ratio of 1.93 (95% CI 1.71-2.17; *P*<.001). This increase in engagement was reflected across multiple platform activities, including self-assessments, goal setting, and content interaction.

However, while these findings validate the effectiveness of nudges and prompts, the study did not explore how individual-level factors shaped these outcomes. Specifically, we did not examine how the intersection of demographic characteristics and cognitive or behavioral phenotypes influenced engagement, if individual engagement followed properties of power laws [61], or if we could leverage economic tools such as the Gini coefficient to plot participation inequality [62].

Understanding these patterns is important for optimizing future interventions for full personalization and maximizing the effectiveness of digital health tools.

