### Randomization

Participants will be randomly assigned to one of the following six arms, as presented in Figure 2:

Arm 1 (baseline control): directive tips only and no to-do checklist.Arm 2: directive tips + social proof tips and no to-do checklist.Arm 3: directive tips + social proof tips + present bias tips and no to-do checklist.Arm 4: directive tips + to-do checklist.Arm 5: directive tips + social proof tips + to-do checklist.Arm 6: gamification (progress bars) + to-do checklist.

Participants will be randomly assigned to one of the six experimental arms using computer-generated randomization in a 1:1:1:1:1:1 ratio. Randomization will be conducted at the point of user registration, ensuring equal probability of assignment to any condition. No stratification or blocking will be used, as randomization is expected to produce comparable groups given the planned sample size. Randomization will be logged automatically by the system to ensure reproducibility and allocation integrity.

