### Power and Sample Size

The primary outcome of interest is engagement, measured through click-through rates, session duration, and to-do checklist completion rates across the 6 experimental arms. These metrics allow us to assess how different combinations of prompts and gamification elements affect user behavior. This will help us determine which strategies are most effective for sustaining participation in self-guided programs.

The study is designed to detect small to moderate effect sizes in engagement differences between intervention groups. Expected effect sizes range from Cohen f=0.1 (small) to f=0.25 (moderate). Our goal is to obtain a power of 80% (β=.20) and a significance level of .05 (α) to ensure adequate sensitivity in detecting meaningful differences between groups.

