### Data Collection

The Evolution Health platform is equipped with a custom data collection interface and reporting mechanism. Data will be collected for each member who is randomly assigned to the experiment, and all data are self-reported. Information on age and self-identified gender will be collected at registration or during secure sign-on across various white-label instances.

The custom database will also track behavioral engagement with each tip and to-do item randomly presented to users, including whether a tip was displayed, whether it was clicked, and whether the user completed the corresponding course component.

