### Engagement Metrics: Operational Definitions

Engagement is defined as follows:

Click rate is defined as tips or checklist items that users click on.Tip interaction is considered “complete” when a user clicks on a tip and completes an exercise.Gamification metrics (eg, progress bar status, quiz completion, badge acquisition) will be recorded as binary variables (earned vs not earned).Session duration is calculated as the elapsed time (in seconds) between a user logging in and logging out of the platform.

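### Click rate is defined in two incompatible ways, and as a pooled proportion it depends on return visits and on a prompt mix that differs by arm

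*Protocol article*

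**What the plan says.** Three sections of the protocol article describe this measure.

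- Primary and Secondary Outcomes makes it a secondary outcome: "click rate, defined as the proportion of tips and checklist items clicked". No denominator is given.
- Engagement Metrics: Operational Definitions says: "Click rate is defined as tips or checklist items that users click on". This is a set or a count, not a proportion.
- Power and Sample Size describes the primary outcome as "engagement, measured through click-through rates, session duration, and to-do checklist completion rates across the 6 experimental arms". A click-through rate is thus part of the primary outcome there, although click rate is secondary in the outcomes section.

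Four other places bear on how a proportion would behave.

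- Behavioral Prompts names the two prompt types as "daily tips and a to-do checklist".
- Data Collection describes a log kept for every prompt shown at random. Its stated contents are: "including whether a tip was displayed, whether it was clicked, and whether the user completed the corresponding course component".
- On timing, the Randomization section states: "Randomization will be conducted at the point of user registration".
- The arm list in the same section gives arms 1 to 3 tips without a checklist, arms 4 and 5 both, and arm 6 a checklist with progress bars and no tips listed.

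**The concern.** A count and a proportion are different outcomes and can move in opposite directions. With both carrying the same name, it is open which one will be compared between arms, and the choice could be made after the data are seen.

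The proportion has a further difficulty. Tips are daily and displays are logged, so items displayed is the natural denominator. It starts at zero at randomization and grows as a user comes back. Bringing users back is one of the effects the arms are meant to have, so the denominator would itself be affected by the assigned arm. Tips and checklist items also had very different uptake in the prior trial, so a pooled rate reflects which prompts an arm offers as well as how users respond to them.

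The measure is meant for inference. The ANOVA sample-size section has engagement metrics compared across six arms, and the Hypothesis section leans on earlier click-through and completion rates.

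**Working it through.** No sample size or power figure in the plan depends on this definition, so there is none to reproduce. The check compares the texts and then illustrates how a pooled proportion behaves.

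**Texts side by side.** The outcomes section gives a ratio without a denominator. The operational definitions give a numerator only. The power section gives a click-through rate at a different rank in the outcome hierarchy. No reading satisfies all three.

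**Inputs, from Our Prior Work.** Tips: 5% clicked, reported for both prior arms that had tips. Checklist: 2.7 of 8 items completed, 2.7/8 = 33.75%.

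**Assumptions.** The denominator is items displayed. All 8 checklist items are shown. Completion stands in for clicks. Checklist uptake stays at 2.7 however many tips, *d*, are shown. The values of *d* are mine.

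**Illustration 1: an arm with tips and checklist (arms 4 and 5 only).** Clicks = 2.7 + 0.05*d*; pooled rate = (2.7 + 0.05*d*)/(8 + *d*).

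| Tips shown | Clicks | Items shown | Pooled rate |
|---|---|---|---|
| 1 | 2.75 | 9 | 30.6% |
| 5 | 2.95 | 13 | 22.7% |
| 10 | 3.20 | 18 | 17.8% |

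Clicks rise by 0.45 (16%) from 1 to 10 tips, while the rate falls by 12.8 percentage points.

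The fall depends on the fixed uptake. At 5 tips, 3.7 checklist items clicked gives (3.7 + 0.25)/13 = 30.4%, almost no fall. At 10 tips, uptake would have to reach 5.0 of 8 to hold the rate: (5.0 + 0.5)/18 = 30.6%.

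**Illustration 2: a tips-only arm.** Take 100 users with 2 displays each at 5%: 10/200 = 5.0%. Add 3 displays per user (300 more), clicked at rate *t*:

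- *t* = 3%: 19/500 = 3.8%
- *t* = 5%: 25/500 = 5.0%
- *t* = 8%: 34/500 = 6.8%

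The rate falls only if later displays are clicked less often than earlier ones. At a constant rate it stays the same although clicks rise from 10 to 25.

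**Illustration 3: prompt mix alone.** Suppose users respond to each prompt type identically in every arm, at the prior rates. With 10 tips and 8 checklist items in the denominator, whether displayed or a fixed list, a tips-only arm scores 5%, an arm with both 17.8%, and a checklist-only arm 33.75%. These differences come from the menu and not from any change in response to a prompt.

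**The case against.** The strongest reply is that the plan never says items displayed. With a fixed list of items as denominator, return visits would not lower the rate, and the prior trial did report its checklist against a fixed 8 items. This stands. The dependence on return visits is conditional on a reading that is well supported but not stated. The dependence on prompt mix does not need that reading.

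A second reply is that this is a condensed article, and an unseen analysis plan may fix the denominator, the window and the handling of users shown nothing. That is fair for those details, and I do not count their absence as an error. It does not cover two conflicting definitions of one named outcome, or the click-through rate appearing under the primary outcome.

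Third, the primary outcome in the outcomes section is already whether a user clicks a prompt, and the prior trial reported tips and checklist items separately. Both are true, so the fix builds on what the team already does.

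A reader might also infer that the prior trial shows a proportion missing a real change, because both tip arms clicked 5% of tips while components completed rose from 1.8 to 2.11. The documents do not support this. The 5% concerns tips only (for example "clicked on 5% of tips and completed an average of 1.8 course components" in prior arm 2), and prior arm 3 added a checklist, which could account for the rise without any change in tip clicking.

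**Conclusion.** The conflict between definitions is exact and needs no assumption. The weakness of a pooled proportion for comparing arms also holds, within limits. It varies with return visits if the denominator is items displayed, and with prompt mix under any denominator if tips and checklist items are pooled.

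The fall from 30.6% to 17.8% shows a possible direction for one user in arm 4 or 5 under fixed checklist uptake. A reader might take it as an expected difference between arms. It is not: the documents give no display counts by arm, and the fall shrinks or vanishes if checklist uptake rises with visits. Nor does it carry over to tips-only arms, where a constant per-display rate leaves the proportion unchanged. How many users would be shown no prompt, and how they would be handled, is not known from this document.

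The point should be corrected before data are analysed. It does not undermine the other outcomes.

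**What to change.** 1. Use one definition of click rate, with its denominator, in Primary and Secondary Outcomes, Power and Sample Size, and Engagement Metrics: Operational Definitions, and give it the same rank in each.
2. For comparing arms, use a measure defined for every randomized user in a fixed window after registration: any prompt clicked, yes or no, with users who have no display or no click counted as no.
3. Keep tips and checklist items separate, and compare each only among arms that offer that type: arms 1 to 5 for tips, and arms 4 to 6 for the checklist, as the arms are listed.
4. Report clicks per display descriptively, by prompt type.

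The cost is wording, since the database is already set up to track engagement with each tip and checklist item. There are three downsides. The per-display percentage is no longer a tested outcome. A window length must be chosen. Any total click count across prompt types needs a caution, because arms offered more prompts can score higher: at the prior rates with 5 tips shown, an arm with a checklist scores 2.95 clicks and a tips-only arm 5 × 0.05 = 0.25.

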### Gamification

The use of game-like elements such as progress bars, badges, and rewards has been shown to increase user motivation and adherence in digital health interventions. These strategies leverage principles of intrinsic motivation, offering visual reinforcement and a sense of accomplishment as users complete tasks. When implemented thoughtfully, gamification can help sustain user engagement over time, especially in self-guided programs.

In our previous work, we explored the application of gamified tools to promote physical activity through a social, multiuser platform. This study highlighted the promise and limitations of these techniques in health behavior change [60]. In the current study, gamification is implemented through a dynamic progress bar that visually tracks user progress, reinforcing engagement through motivational feedback, and awarding badges for completing sessions and passing session quizzes.

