### The Intervention

Shared Strength (Спільна Сила) is a self-guided interactive behavior change treatment course based on traditional evidence-based treatments (Table 2). It draws from multiple therapeutic frameworks, including CBT, motivational interviewing, and social cognitive theory. The goal is to provide users with a flexible, culturally sensitive, interactive course that supports emotional resilience and behavior change.

Other interactive courses in the Evolution Health platform have been extensively examined in the literature [10,23,24,61,62,68-90]. Shared Strength mirrors its structure and design (Table 3). This consistency enables us to leverage existing platform infrastructure and previous research insights while applying new engagement strategies.

**Table 2 table2:** Theoretical constructs and evidence-based components.

Theoretical construct	Shared Strength (Спільна Сила)
Brief intervention	✓
Cognitive behavioral therapy	✓
Gamification	✓
Health belief model	✓
Motivational interviewing	✓
Social cognitive theory	✓
Targeting and tailoring	✓

**Table 3 table3:** Main course components.

Course component	Shared Strength (Спільна Сила)
Avatar upload	✓
Course completion certificate	✓
Course worksheets	✓
Gamified CBT^a^ course	✓
Getting started video	✓
Goals exercise	✓
Moderated community	✓
Private messaging	✓
Statistics extranet (for corporate clients)	✓
Tailored depression and anxiety test	✓
Therapist extranet	✓

^a^CBT: cognitive behavioral therapy.

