### Course Content Overview

Shared Strength (Спільна Сила) contains nine interactive sessions. Each session is designed to foster emotional resiliency using evidence-based strategies drawn from CBT, behavior change theory, and supportive self-help principles. The structure allows participants to move at their own pace while reinforcing learning and self-efficacy. Key session themes include (1) understanding emotional responses to displacement, (2) managing anxiety and low mood, (3) setting personal goals and building hope, (4) practicing mindfulness and grounding techniques, and (5) strengthening connections and community.

Each session includes short readings and interactive tools, such as goal setting, a resiliency diary, to-do checklists, and a summary quiz to reinforce learning. Users progress at their own pace.

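### Secondary outcome 4 includes badges, but the protocol does not settle whether arms 1 to 5 can earn them; if only arm 6 can, comparisons using badges favour arm 6 by construction

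*Protocol article*

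**What the plan says.** All places are in the protocol article.

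- **Primary and Secondary Outcomes.** The fourth secondary outcome is "number of course sessions completed, including badge acquisitions and quiz completions". No rule says how the three items are combined.
- **Gamification (Introduction).** The component has two parts. First, "In the current study, gamification is implemented through a dynamic progress bar that visually tracks user progress"; second, "awarding badges for completing sessions and passing session quizzes". No arm is named.
- **Randomization.** Of the six arms, only one lists gamification: "Arm 6: gamification (progress bars) + to-do checklist". Badges are not mentioned.
- **Multiarm Trial Rationale.** The fifth tested component is "gamification, which builds intrinsic motivation through visual indicators of advancement and progress feedback".
- **The Intervention, Tables 2 and 3.** Gamification and a "Gamified CBT^a^ course" are ticked for Shared Strength as a whole, without restriction by arm.
- **Course Content Overview.** There are nine sessions, and each contains "a summary quiz to reinforce learning", so quizzes are course content in every arm.
- **Engagement Metrics: Operational Definitions.** "Gamification metrics (eg, progress bar status, quiz completion, badge acquisition) will be recorded as binary variables (earned vs not earned"). Again no arm is named.

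**The concern.** The fourth secondary outcome should show how far users progress through the nine sessions. A badge is the platform's reward for a session completed or a quiz passed. If the reward belongs to one randomized arm and also enters the outcome, that arm is credited with its own treatment, and users in the other arms cannot score on that part whatever they do.

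The direction matters because the Hypothesis section names arm 6 among the arms expected to show higher engagement. The behavioral data are also meant to train the personalization models, so an arm difference produced by scoring could be carried forward as if it were behavior. With no combining rule stated, the choice could also be made after the data are seen.

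A smaller conflict concerns coding. This outcome is called a number, yet quiz completion and badge acquisition are to be recorded as earned or not earned. If that means one flag per user, a user with 1 of 9 quizzes and a user with 9 of 9 look the same. If it means one flag per quiz or badge, a count can be recovered. The text does not say which.

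**Working it through.** The protocol gives no figure for this outcome, so there is none to reproduce. The check takes two users with identical course use and scores them under each reading the text allows.

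**Inputs from the document.** Nine sessions, each with a quiz (Course Content Overview); badges for completing sessions and for passing quizzes (Gamification); gamification in arm 6 only, among the listed arms (Randomization).

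**Assumptions.** The user completes k sessions and passes the k matching quizzes. Where items are added, each counts 1. The number of badges per session is not stated, so two cases are shown: one badge per session, or one for the session and one for its quiz.

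**Reading A: badges only in arm 6, added to the count.**

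- Arms 1 to 5: sessions + quizzes = k + k = 2k.
- Arm 6, one badge per session: k + k + k = 3k. Ratio 3k / 2k = 1.5.
- Arm 6, session badge and quiz badge: k + k + k + k = 4k. Ratio 4k / 2k = 2.

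| k | Arms 1 to 5 | Arm 6, one badge per session | Arm 6, two badges per session |
|---|---|---|---|
| 1 | 2 | 3 | 4 |
| 3 | 6 | 9 | 12 |
| 9 | 18 | 27 | 36 |

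**Reading B: badges only in arm 6, compared as a separate measure.** Arms 1 to 5 score 0 for every k. The contrast with arm 6 shows who was allocated badges, not who used the course more.

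**Reading C: badges in all arms, added.** Every arm scores 3k or 4k, so the difference between arms for identical use is 0. The result is no longer a number of sessions: at k = 9 it is 27 or 36.

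**Reading D: badges and quizzes only mark a session as complete.** The score is k in every arm. The difference is 0, and the badge adds nothing to the session record.

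**With badges left out.** The score is k if only sessions are counted, or 2k if quizzes are added, in all six arms. Identical use gives identical scores.

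**Which reading does the text support?** The Gamification section, the arm list and the Multiarm Trial Rationale, taken together, make gamification a randomized component that includes badges; this points to A or B. Tables 2 and 3, and the words in parentheses in arm 6's label, point to C or D. No sentence decides between them.

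**The case against.** The strongest reply is that badges may well be available to everyone, with only the progress bar varying by arm. Arm 6's label names progress bars alone, the tested component is described through visual progress feedback, the gamification example in Table 1 is a progress bar, and Tables 2 and 3 tick gamification for the whole course. The definitions section files quizzes under gamification metrics although every session has a quiz, so that label cannot by itself mean arm 6 only. This stands, and it is why the point is conditional.

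It can also be said that nothing in the outcome's wording calls for a sum. Badges and quizzes may be companion measures under one heading, or markers that a session was completed. That stands too: the 1.5 to 2 ratio belongs to an assumed additive score. It does not rescue badges as a between-arm measure, because under separate reporting a badge limited to arm 6 still leaves the other arms at zero.

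A reader might infer that arm 6 will score higher for the same use, or that its hypothesis would be confirmed by scoring alone. The document supports neither. Both need badges to be limited to arm 6. The hypothesis is not tied to this outcome, and the first secondary outcome already covers session completion without mentioning badges. The primary outcome is clicking on tips or checklist items and does not use badges.

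Finally, a condensed article may leave derivation detail to a fuller plan. That would excuse silence. Here the article itself puts badges into the outcome and describes gamification in ways that do not agree.

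**Conclusion.** The point holds in conditional form. The article includes badges in a between-arm secondary outcome and does not settle whether five of the six arms can earn them.

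If badges are limited to arm 6, the comparison is biased toward arm 6 by construction: by a factor of about 1.5 to 2 for identical use if badges are added (assuming each completed session has its quiz passed), or through structural zeros in arms 1 to 5 if badges are compared separately. If badges exist in all arms, or only mark completion, the arm bias is nil and the badge term is redundant. Under none of these readings does it add information on session completion.

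The consequence is limited to a secondary outcome. It is still worth correcting before data are analyzed, because the possible bias favours an arm that the protocol expects to do well.

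**What to change.** 1. Define the fourth secondary outcome as the number of distinct course sessions completed, 0 to 9, derived in the same way in all six arms.
2. Report the number of session quizzes completed as a separate count, and make clear under Engagement Metrics: Operational Definitions that it is not one yes/no flag per user.
3. Keep badge acquisition and progress bar status out of between-arm outcomes. Report them descriptively, as delivery of gamification, in the arms that have them.
4. Reconcile the Gamification section, Tables 2 and 3, the arm list under Randomization, the outcome definition and the operational definitions, so that they state which arms have badges.

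The cost is wording. Session completion is already required by the first and fourth secondary outcomes, and quiz completion is already to be recorded, so no extra participants or new measurements are needed. The platform log must hold quizzes individually, or as a count, rather than as a single flag.
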